## Abstract

**Background:**

Nonmotor symptoms of Parkinson disease are a major factor of disease burden but are often underreported in clinical appointments. A digital tool has been developed to support the monitoring and management of nonmotor symptoms.

**Objective:**

The aim of this study is to establish evidence of the impact of the system on patient confidence, knowledge, and skills for self-management of nonmotor symptoms, symptom burden, and quality of life of people with Parkinson and their care partners. It will also evaluate the usability, acceptability, and potential for adoption of the system for people with Parkinson, care partners, and health care professionals.

**Methods:**

A mixed methods implementation and feasibility study based on the nonadoption, abandonment, scale-up, spread, and sustainability framework will be conducted with 60 person with Parkinson–care partner dyads and their associated health care professionals. Participants will be recruited from outpatient clinics at the University Hospitals Plymouth NHS Trust Parkinson service. The primary outcome, patient activation, will be measured over the 12-month intervention period; secondary outcomes include the system’s impact on health and well-being outcomes, safety, usability, acceptability, engagement, and costs. Semistructured interviews with a subset of participants will gather a more in-depth understanding of user perspectives and experiences with the system. Repeated measures analysis of variance will analyze change over time and thematic analysis will be conducted on qualitative data. The study was peer reviewed by the Parkinson’s UK Non-Drug Approaches grant board and is pending ethical approval.

**Results:**

The study won funding in August 2021; data collection is expected to begin in December 2022.

**Conclusions:**

The study’s success criteria will be affirming evidence regarding the system’s feasibility, usability and acceptability, no serious safety risks identified, and an observed positive impact on patient activation. Results will be disseminated in academic peer-reviewed journals and in platforms and formats that are accessible to the general public, guided by patient and public collaborators.

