### Aims and Objectives

The study will assess the impact of NMS Assist on people with Parkinson disease, their care partners, and their Parkinson care team. Evidence regarding the system’s perceived impact on knowledge, confidence, and skills at managing NMS and its safety, acceptability, and usability will improve the product design and determine readiness for advancement for wider adoption.

To achieve this aim, there are 5 key objectives:

Assess the impact of the NMS Assist system on patient activation, symptom burden, and quality of life in people with Parkinson and their care partnersExamine the impact of the NMS Assist system on contact between people with Parkinson disease and HCPsAssess the acceptability and usability of the system and identify any barriers to use for people with Parkinson, their care partners, and health care professionalsAssess the cost impacts of the system compared to the standard of careEstablish whether there is sufficient evidence of the impact of NMS Assist on the knowledge, confidence, and skills of people with Parkinson disease managing NMS, the identification of new or problematic NMS, and the prompting of health care contacts to justify more extensive trials

Based on evidence gathered from previous studies and our understanding of state of the art concerning digital health technologies and ongoing work with digital tools used with people with Parkinson disease, we hypothesize the following:

NMS Assist will be acceptable, accessible, and engaging for usersUse of NMS Assist will be feasible within an NHS serviceNMS resources will have a positive impact on patient activation (knowledge, skills, and confidence)

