### Sample Size

We will recruit 60 people with Parkinson disease–care partner dyads and their associated HCPs—the exact number of HCPs cannot be determined until the people with Parkinson disease–care partner dyads have been recruited, as we will include HCPs who are associated with those patients. Of the 60 dyads, at least 20 people with Parkinson disease–care partner dyads will be purposively sampled for a semistructured interview. We will also be inviting the HCPs associated with those dyads to separate semistructured interviews.

Since this is a feasibility study, a formal sample size calculation has not been performed. A sample size of 60 people with Parkinson disease–care partner dyads was selected because this is an achievable number of patients to recruit within the study period based on our prior research.

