### Outcomes

#### Primary Outcome

The primary outcome, patient activation, will be assessed using the Patient Activation Measure [17]. The concept of patient activation refers to patients having the necessary knowledge, confidence, and skills to manage their own health and well-being. It is important to note that as this study design is centered on feasibility, the evidence captured will not measure efficacy. Should there be indications of a positive impact of the NMS Assist system on patient activation and health and well-being outcomes, efficacy will be tested in further studies.

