### Data Analysis

The primary analysis will be the comparison of mean Patient Activation Measure scores [17] at each month. A repeated measures analysis of variance will be conducted to identify any significant changes in mean Patient Activation Measure scores over the 13 time points (baseline and monthly until 12-months postbaseline). If the normality assumption for a repeated measures analysis of variance is not met, a nonparametric alternative will be used.

The same analysis for the primary outcome will be conducted for the health and well-being outcome measures and the System Usability Scale, comparing the measure scores at the baseline, midpoint, and end points. Exploratory analyses will be conducted to identify potential associations between demographic or disease characteristics and outcome measures to inform hypotheses for future evaluations. All other quantitative data will be analyzed using descriptive statistics.

Semistructured interviews will be coded by 2 investigators using thematic analysis [40]. Triangulation of the quantitative questionnaire, system use, and qualitative semistructured interview data will be conducted to validate findings.

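### The activation success criterion is directional but undefined, and the only stated primary test is non-directional and gives no estimate of change

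*Protocol article*

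**What the plan says.** **Success criterion.** The Conclusions paragraph of the Abstract lists what will count as success. Beside feasibility, usability, acceptability and the absence of serious safety risks stands "an observed positive impact on patient activation". No month, summary, size or interval is attached.

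**Primary analysis.** Data Analysis states: "The primary analysis will be the comparison of mean Patient Activation Measure scores", month by month. A repeated measures ANOVA is then used "to identify any significant changes in mean Patient Activation Measure scores over the 13 time points". If normality fails, "a nonparametric alternative will be used"; it is not named. No contrast, trend or change estimate is singled out.

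**Use of the result.** Aims and Objectives hypothesises a positive effect on activation. Its fifth objective asks whether the evidence on knowledge, confidence and skills, on symptom identification and on "the prompting of health care contacts to justify more extensive trials" is sufficient. Primary Outcome says that signs of a positive impact would lead to efficacy testing in later studies, and that "the evidence captured will not measure efficacy".

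**Size.** Sample Size gives 60 dyads in a single group and says that "a formal sample size calculation has not been performed". No alpha, SD, correlation or dropout rate is given.

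**The concern.** The criterion needs a direction and some idea of size. The test fixed as primary supplies neither. An omnibus test on 13 means responds to any departure from a flat profile: a rise, a fall, or a mid-year bump that is gone by month 12. A significant result therefore need not support the criterion, and a non-significant one does not say what change was seen.

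Because the criterion names no month or summary, whoever writes the report can decide afterwards whether positive means month 12, the average of follow-up, every month or some month. The result feeds a judgement on whether larger trials are warranted, so the reader of the final paper should know beforehand what would and would not count.

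**Working it through.** The plan gives no power or error figure, so there is none to reproduce. The check asks how often the activation criterion would be met with no true change under the readings its wording allows, and whether the ANOVA can tell a rise from a fall.

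**Inputs.** From the protocol article: 13 time points, 60 participants, one group. Assumed, because not stated: two-sided 5% level; 60 or 45 with complete data; within-person correlation of 0.5-0.7 (compound symmetry) or AR(1) with 0.9 between adjacent months; effects in SD units. Simulations used 4,000 runs per scenario and a Greenhouse-Geisser correction.

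**1. Chance of meeting the criterion with no true change**

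| Reading of the criterion | Probability |
|---|---|
| Corrected F test significant and month 12 above baseline | 0.014-0.027 |
| All 12 months above baseline | 0.07-0.14 |
| Month 12, or the follow-up average, above baseline | 0.50 (simulated 0.49-0.53) |
| At least one of 12 months above baseline | 0.86-0.93 |

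Three rows can be checked by hand.
- Sign of one mean change: 1 − Φ(0) = 0.50 for any n or SD, if the mean change is symmetric about 0.
- All months higher, compound symmetry: the 13 means are exchangeable, so baseline is the lowest with probability 1/13 = 0.077.
- Any month higher, compound symmetry: 1 − P(baseline is the highest) = 1 − 1/13 = 12/13 = 0.923.

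AR(1) 0.9 gives the other ends of the last two ranges, about 0.14 and 0.86.

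**2. Direction.** Under compound symmetry the power of the F test depends on λ = n·Σ(μj − μ̄)²/(1 − ρ), in SD units. For a linear change of 0.3 SD over months 0 to 12, Σ(μj − μ̄)² = 0.3² × 182/144 = 0.11375. With n = 60 and ρ = 0.6, λ = 60 × 0.11375/0.4 = 17.06. The deviations are squared, so +0.3 and −0.3 give the same λ and the same power. Simulated rejection rates for a rise and a fall agree with this apart from simulation error: 0.73 and 0.75 (ρ = 0.6), 0.39 and 0.40 (AR(1) 0.9).

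**3. A single contrast instead.** If a positive change were claimed only when the two-sided 95% CI for month 12 minus baseline lies wholly above 0, the chance with no true change would be 2.5% (simulated 2.3-3.0%). The half-width is t(0.975, n−1) × √(2(1 − ρ)/n):
- n = 60: 2.001 × √(1.0/60) = 0.26 SD at ρ = 0.5; 2.001 × √(0.6/60) = 0.20 SD at ρ = 0.7.
- n = 45: 2.015 × √(1.0/45) = 0.30 SD at ρ = 0.5; 2.015 × √(0.6/45) = 0.23 SD at ρ = 0.7.

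**4. Power of the contrast against the ANOVA (n = 60, true change 0.3 SD).** For a linear rise over six assumed correlation structures, the contrast has 37-84% and the corrected ANOVA 28-88%. The contrast is higher in four of the six and slightly lower in the two with compound symmetry. For an early plateau, over a similar set of six, the ANOVA has 26-70% and the mean of months 1-12 minus baseline has 54-87%.

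**The case against.** **This is a feasibility study that disclaims efficacy.** Primary Outcome says so, and Strengths and Limitations concedes that there is no comparison group. That is fair: using an indicative signal to motivate a later trial is compatible with not claiming efficacy, and the disclaimer does not contradict the criterion. But the plan itself makes a significance test the primary analysis and a positive result a mark of success. The disclaimer does not say how that result is to be judged.

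**Contrasts and intervals belong in an SAP.** Often they do, and a missing detail alone would be no finding. Here the article fixes a non-directional test for a directional criterion. An SAP that only elaborated that test would inherit the mismatch.

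**The monthly means show direction and size.** This stands. A reader might infer that the analysis cannot reveal direction at all; the 13 means will do so descriptively. What is missing is a named contrast, its interval and a rule for judging it.

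**A falling profile could pass as success.** A reader might infer this, because with a true linear fall of 0.3 SD at least one month still lies above baseline in 51-68% of simulated studies. But the protocol does not adopt the any-month reading, a fall is not a positive impact in ordinary words, and with all 13 means compared a selective choice would be visible.

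**Activation is not a sole go/no-go rule.** Correct. The other success criteria must also be met, and the fifth objective draws on symptom identification and health care contacts as well.

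**Conclusion.** The point holds in this limited form: the activation criterion is directional but undefined, the only primary test is non-directional and yields no estimate of change, and no text connects them. With no true change, the chance of meeting the criterion runs from about 2% to 93% depending on the reading chosen. That spread is the defect.

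A reader might infer that the study would be declared a success half the time by chance. The protocol does not support that. The 50% needs an assumed sign rule on one mean change, which the text does not state, and it concerns one of several joint criteria.

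Apart from the 50% and the two compound-symmetry fractions, which are exact, the rates rest on the assumed correlations and on 45-60 complete participants. The symmetry of the F test between rise and fall does not depend on those choices. Nothing here prevents the study from running, but the wording should be settled before the data are seen.

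**What to change.** In Data Analysis, prespecify one primary contrast: the mean change in patient PAM score from baseline to month 12, reported with a 95% CI. Keep the ANOVA and the other months as supportive or descriptive.

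In the Abstract, tie the activation criterion to that estimate and its interval. Report a positive change as shown only when the interval lies above 0; otherwise report it as an indication, with its uncertainty. Call it change over 12 months rather than impact, since there is no comparator.

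**Cost.** Wording only: no new data, visits or participants. The criterion becomes somewhat harder to meet. With a true linear rise of 0.3 SD, the interval would exclude 0 in 37-84% of studies, so it would miss the rise in 16-63%. That is why an interval covering 0 should be reported as an indication and not as failure. Power relative to the ANOVA depends on the shape of change: similar or better for a linear rise under most assumed correlations. If the team expects an early plateau, the mean of months 1-12 minus baseline is the stronger contrast. Either will serve if it is named in advance.

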**Trial Registration:**

ClinicalTrials.gov NCT05414071; https://clinicaltrials.gov/ct2/show/NCT05414071

**International Registered Report Identifier (IRRID):**

PRR1-10.2196/40317

## Introduction

### Background

The aging population of the United Kingdom is expected to nearly double the prevalence of Parkinson disease by 2065 [1]. Parkinson disease significantly impacts patients, their care partners and families, and the health system of the United Kingdom. However, people with Parkinson disease are not monitored continuously or even frequently [2]; the National Institute for Health and Care Excellence guidelines currently recommend that people with Parkinson disease be reviewed every 6 to 12 months [3]. Nonmotor symptoms (NMS) of Parkinson can increase disease burden and decrease quality of life [4,5] but are often overlooked or undeclared in routine appointments [6]. Digital technology has the potential to improve the identification of NMS and enable more timely and appropriate treatment.

In this study, we will build on this evidence to implement improvements to a digital self-management system for nonmotor symptoms (NMS Assist) and to examine the impact of NMS Assist on patient activation and remote NMS monitoring (specifically the health care contacts triggered by that monitoring using NMS Assist). The high proportion of the UK population with internet access [7] means that this intervention could easily be made available on a large scale to people with Parkinson disease and their care partners.

### Rationale

#### Benefits for People With Parkinson Disease and Care Partners

NMS Assist is expected to have several benefits for people with Parkinson disease and care partners; notably, by improving symptom monitoring by making assessments more timely, relevant, and convenient, by increasing disease and symptom awareness, and by supporting people with Parkinson disease and care partners in managing their NMS at home. A formative usability evaluation of 13 users (9 people with Parkinson disease, 4 care partners) demonstrated satisfaction with the system (System Usability Score 80%) [8].

The usability study identified 11 critical issues for improvement, centered on 3 themes: navigation, content, and accessibility [8]. These aspects of the system were subsequently refined based on participants’ suggestions. To reduce the length of the NMSQ, people with Parkinson disease can complete partial assessments to monitor their symptoms. However, they are asked to complete the length of the Nonmotor Symptoms Questionnaire (NMSQ) every 6 months to ensure that a holistic assessment is performed, providing clinical safety netting.

#### Benefits for Health Care Professionals

NMS Assist will identify unmet need among people with Parkinson disease, and the adoption of a new system will add an element to the workload of health care professionals (HCPs); new skills will be needed to make clinical decisions based on the data developed. However, NMS Assist will provide HCPs with the ability to monitor and prioritize their patients efficiently. The main long-term benefit is the development of shared responsibility of health management with people with Parkinson disease, achieving the ambitions of the National Health Service (NHS) Long Term Plan with digitally enabled care and delivery of predictive, personalized, preventive and participatory care medicine, with improved support for care partners [9]. In time, this may result in fewer NMS-related complications (eg, falls), hospitalizations, and institutionalized care.

#### Benefits for Parkinson Disease Research

Ongoing collection of data will enable a longitudinal database. This will enable evaluations to identify clusters of NMS and associations between NMS and people with Parkinson disease and care partner characteristics. The value of this database for research would only be increased if NMS Assist was adapted and adopted in countries worldwide. For instance, it would enable examining global similarities or differences in symptoms and symptom clusters, quality of life impairment, and impact on care partners.

### Theoretical Frameworks

The nonadoption, abandonment, scale-up, spread, and sustainability (NASSS) framework [10] that aims to help predict and evaluate the impact of digitally enabled health programs was used to support the conception and development of the study plan. It was chosen as the main theoretical framework to ensure that the evaluation would examine a holistic set of variables essential to the long-term success and sustainability of the NMS Assist system. Qualitative data will be collected through semistructured interviews with a subset of users structured according to the theoretical framework of acceptability [11]. The use of both quantitative and qualitative methods to evaluate usability will enable the data to be triangulated.

These 2 frameworks will form the theoretical basis for the evaluation of NMS Assist:

Long-term adoption and suitability to further trials will be evaluated using the NASSS framework [10]. This framework is important to include because interventions can only add value if they are successfully adopted and used. This framework emphasizes the consideration of the multiple levels—individuals and systems—that influence adoption and nonadoption.The theoretical framework of acceptability will be used to structure the semistructured interview guide [11]. This framework was chosen because it was developed specifically for health interventions, captures a multifaceted view of acceptability (with 7 components), and emphasizes the importance of considering different time points when evaluating acceptability [11].

### Research Question

The main research question for the study is as follows: How does a digital remote monitoring and education system (NMS Assist) impact patient activation, symptoms, and quality of life for people with Parkinson disease and care partners?

### Aims and Objectives

The study will assess the impact of NMS Assist on people with Parkinson disease, their care partners, and their Parkinson care team. Evidence regarding the system’s perceived impact on knowledge, confidence, and skills at managing NMS and its safety, acceptability, and usability will improve the product design and determine readiness for advancement for wider adoption.

To achieve this aim, there are 5 key objectives:

Assess the impact of the NMS Assist system on patient activation, symptom burden, and quality of life in people with Parkinson and their care partnersExamine the impact of the NMS Assist system on contact between people with Parkinson disease and HCPsAssess the acceptability and usability of the system and identify any barriers to use for people with Parkinson, their care partners, and health care professionalsAssess the cost impacts of the system compared to the standard of careEstablish whether there is sufficient evidence of the impact of NMS Assist on the knowledge, confidence, and skills of people with Parkinson disease managing NMS, the identification of new or problematic NMS, and the prompting of health care contacts to justify more extensive trials

Based on evidence gathered from previous studies and our understanding of state of the art concerning digital health technologies and ongoing work with digital tools used with people with Parkinson disease, we hypothesize the following:

NMS Assist will be acceptable, accessible, and engaging for usersUse of NMS Assist will be feasible within an NHS serviceNMS resources will have a positive impact on patient activation (knowledge, skills, and confidence)

## Methods

### Study Design

This investigation will be a mixed methods feasibility study using an implementation science theoretical framework [12] to examine the research question. Quantitative methods will be used to evaluate NMS Assist’s impact on patient activation as well as to examine health and well-being outcomes, usability, and engagement. Qualitative methods, specifically semistructured interviews, will also be used to gather a more in-depth understanding of the acceptability, usability, and engagement of users with NMS Assist (see Figure 1 for an overview). The SPIRIT (Standard Protocol Items: Recommendations for Interventional Trials) checklist was used to ensure the proposal was meeting content and quality standards (Multimedia Appendix 1) [13].

**Figure 1 figure1:**
[figure not shown]
Study sequence diagram. NMS: Nonmotor symptoms. PwP: People with Parkinson disease. MDS-NMS: Movement Disorder Society–Nonmotor Rating Scale. PDQ-39: Parkinson’s Disease Questionnaire–39. WEMWBS: Warwick-Edinburgh Mental Wellbeing Scale.

